## Abstract

**Background:**

The mass colorectal cancer screening program was implemented in 2008 in France, targeting 16 million French people aged between 50 and 74. The current adhesion is insufficient and the participation rate is even lower among the underserved population, increasing health inequalities within our health care system. Patient Navigation programs have proved their efficiency to promote the access to cancer screening and diagnosis.

**Methods/Design:**

The purpose of the study is to assess the implementation of a patient navigation intervention that has been described in another cultural environment and another health care system. The main objective of the program is to increase the colorectal cancer screening participation rate among the deprived population through the intervention of a navigator to promote the Fecal Occult Blood Test (FOBT) and complementary exams.

We performed a multisite cluster randomized controlled trial, with three groups (one experimental group and two control groups) for 18 months.

**Discussion:**

The study attempts to give a better understanding of the adhesion barriers to colorectal cancer screening among underserved populations. If this project is cost-effective, it could create a dynamic based on peer approaches that could be developed for other cancer screening programs and other chronic diseases.

**Trial registration:**

NCT02369757

## Background

Colorectal cancer (CRC) is the third most common cancer diagnosed and the second leading cause of cancer death in both men and women in France, according to the GLOBOCAN estimates [1]. Approximately, 42 000 new cases were diagnosed in 2012, predominantly men and 17 500 deaths were attributed to CRC [1].

Since 2008, CRC mass screening has been implemented in France. This population-based program targets men and women aged from 50 to 74 who receive a standardized invitation letter, every 2 years, to encourage them to consult their general practitioner (GP). The GP delivers a screening test. People who don’t send their test to the screening center receive a reminder letter. They then receive the test at home within 6 months following the date of the first invitation. The test used is the FOBT, followed by a colonoscopy in case of a positive test result.

Several studies have universally shown that FOBT, followed by colonoscopy in case of a positive test result can reduce CRC mortality [2–6]. But to be efficient, a high participation of the target population is required for these screening programs, at least 50 % [7].

In France, for the period 2009–2010, 17 million French people were invited to participate in the CRC screening program. The national participation rate was only 33.8 % (5.14 million) whereas the national objective was to reach a participation rate of 60 % in 2013. Significant disparities were recorded. The women participated more than the men (36.5 % vs. 31.4 %). Among men, older people (over 70) participated more than the younger ones. Women between 60 and 64 years old, participated more. Moreover, participation rates varied widely according to the regions.

The factors affecting FOBT screening program participation have been analyzed. Gender, age, marital status, educational status, social status and economical status can influence participation [8]. In France, the correlation between socioeconomic status and participation rate has been observed [9].

It is interesting to note that France is one of the Western European countries where socioeconomic gradient – measured by the educational status – has the highest impact on mortality [10]. Moreover, social inequalities impact cancer rates, including colorectal cancer [11]. As a matter of fact, France is one of the European countries where educational status, among all risk factors considered, has the highest impact on cancer mortality.

Patient Navigation (PN) is a patient-centered healthcare service delivery model that centers on reducing barriers to cancer care [12–15]. The first “Patient Navigation” program was established in New York in the early 1990s, by Freeman, a surgical oncologist at Harlem Hospital [15]. The development of the PN concept was related to the findings of the American Cancer Society National Hearings on Cancer in the Poor (Program No Need to Die). Based on these hearings, the first PN program was built. It focused on the critical window of opportunity to save lives from cancer by eliminating barriers to timely diagnosis and treatment for low-income populations [16]. The program was composed of navigators who were from the community or culturally similar to the population served. The patient navigator was defined as an individual who could educate and empower patients, serving as their advocate in navigating the health care system. This intervention succeeded in improving access to breast and colorectal cancer screening for the deprived population. It helped improve survival rates by 5 years [17, 18]. Moreover, this approach is considered as an effective means to reduce inequalities in the USA [19]. These interventions have been increasingly adopted throughout the Unites States, Canada [20] and China [21, 22].

We hypothesize that inequalities generated by general prevention measures can be offset with specific measures, thanks to peer education which targets population from underserved areas.

The primary objective of this study is to determine effectiveness of a PN Program on CRC screening participation among the underserved population.

The secondary aims are: 1) to perform a realistic evaluation of an innovating intervention, of which the effectiveness has been demonstrated by several randomized studies in another health care system 2) to assess the implementation into a specific context 3) to identify factors favoring or hindering the effectiveness of the intervention.

The purpose of this article is to describe the protocol of this study.

## Methods/Design

### Study design

COLONAV is a population-based cluster randomized control study. It assesses the effectiveness of an intervention previously described and evaluated in another cultural environment and in another health care system, as regards CRC screening attendance.

Three parallel groups will be compared:one experimental group with interventiontwo control groups without intervention

### Selection of study sites and participants

The study will include men and women aged from 50 to 74 years old, invited to screening and living in underserved areas. The research will be conducted in the following five districts because of their different socioeconomic characteristics:A rural district (L’Ardèche, 313 578 inhabitants)A district with an industrial economy and low development (La Loire, 746 115 inhabitants)A district with a tertiary economy and high development (Le Rhône, 1 708 671 inhabitants)A district where CRC screening has been implemented for a long time (La Côte d’Or, 524 144 inhabitants)One of the suburban districts of the capital (Le Val-de-Marne, 1 318 537 inhabitants)

In each district, the geographical areas to be studied will be determined by matching the criteria in terms of the socioeconomic indicators and the low participation rate for CRC screening. In France, each district is divided into IRIS zones, ie aggregated units for statistical information used as a system for dividing the country into units of equal size (2000 residents per basic unit). We will use the French European Deprivation Index (EDI) [23] to determine the most deprived IRIS zones (quintiles 4 and 5 of the Index corresponding to the most disadvantaged areas) and the participation rates of each zone to select the lowest ones.

### Sample size

We estimated that the intervention would be relevant if it provided an 8 % absolute increase in the colorectal cancer screening participation rate (22 % in the control group and 30 % in the intervention group). With a two-sided α risk of 0.05 and a β risk of 0.1, and assuming an intraclass correlation coefficient for clusters of 0.004 and a mean of 500 patients per cluster (assuming an average of 2000 people per IRIS zone and percentage of people between 50 and 75 years equal to 25 % of the total population), we needed 4 clusters per group (2000 people per group). Taking into account the three groups (one intervention group and two control groups) and stratified by department gives a total number included about 30 000 individuals.

We establish that the number of IRIS zones needed to meet the objectives of the study is 20 intervention IRIS zones and 40 control IRIS zones [24].

So, for each district, we will randomly select:four contiguous intervention IRIS zoneseight control IRIS zones divided into two groups (one adjacent and one distant from the intervention group)

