#### Recruitment and training of navigators

The strategy is to recruit and train one navigator per district. Candidates’ recruitment will be done by means of job description that will be widely diffused. The profile desired is a peer, i.e. a person corresponding to the target population of the study, living in the intervention zones. The district committees of “La Ligue contre le Cancer” (a French non-governmental organization which promotes cancer screening, gives support to patients and funds research, will be in charge of recruiting each navigator). Navigators will receive formal training for one week on all issues related to the following: the navigation process, cancer generalities, CRC screening, counseling and support to patients as needed.

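### The sample size counts IRIS zones as independent clusters, but the intervention is placed in one contiguous four-zone block per district with one navigator, so power and inference should rest on about five blocks per group

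*Protocol article*

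**What the plan says.** All sizing inputs are in the Sample size section of the protocol article:

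- Error rates: "With a two-sided α risk of 0.05 and a β risk of 0.1".
- Participation: "22 % in the control group and 30 % in the intervention group".
- Clustering: "assuming an intraclass correlation coefficient for clusters of 0.004" with "a mean of 500 patients per cluster", the cluster being an IRIS zone.
- Result: "we needed 4 clusters per group (2000 people per group").
- Scaling up: three groups, "stratified by department gives a total number included about" 30 000 people, that is 20 intervention and 40 control zones.

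The same section then fixes the layout: "So, for each district, we will randomly select:four contiguous intervention IRIS" zones, plus eight control zones in two sets, one next to the intervention set and one far from it. Under Recruitment and training of navigators: "The strategy is to recruit and train one navigator per district".

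The Primary outcome and Quantitative analysis sections compare before/after change in participation between intervention and control areas, by logistic regression with a period-by-area interaction.

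**The concern.** The sizing treats each zone as a separate cluster that contributes its own information. The layout removes that independence on the intervention side. Four adjoining zones are taken together, share one navigator, and fix where the adjacent and distant control sets can lie. Anything particular to that neighbourhood or that navigator moves all four zones together, and an ICC defined for a single zone does not capture it.

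Two things are at stake. First, stated power: 20 zones per group look like a large surplus, but the surplus disappears if the unit is the block. Second, validity: an analysis that takes zones, or individuals, as independent would understate the standard error of the intervention effect. A lesser issue is that the figure of 4 clusters comes from a normal approximation, which is optimistic with so few clusters.

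**Working it through.** **1. The plan's own figure.** Inputs are 0.22 v 0.30, two-sided 0.05, power 90%, ICC 0.004 and 500 per zone, all from Sample size.

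- Individuals per group, unpooled: (1.96 + 1.2816)² × (0.22×0.78 + 0.30×0.70) / 0.08² = 627. The pooled formula gives 630, and 655 with continuity correction.
- Design effect: 1 + 499 × 0.004 = 2.996.
- Clusters: 627 × 2.996 / 500 = 3.75; for the other two, 3.77 and 3.92. All round up to 4. Nominal power with 2000 per group is 91.6%. The figure reproduces.

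**2. Small-sample check of 4 v 4.** The sum of the two variances is 0.1716 + 0.21 = 0.3816. Noncentrality = 0.08 / √(0.3816 × 2.996 / 2000) = 3.346. Against t on 6 df, power is 79.5% (79.6% by beta-binomial simulation with a t-test on cluster proportions). For 5 v 5, on 8 df, it is 90.4% (90.2% simulated).

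**3. Pooled trial, zones independent.** 20 v 20 zones at ICC 0.004 gives power above 99.9%.

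**4. Pooled trial, five blocks of 2000 per group.** The block ICC is not given, so the values below are assumptions. 4 df corresponds to district pairing with no precision gain assumed, and 8 df to an unpaired comparison.

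- Post-only noncentrality = 0.08 / √(0.3816 × DE / 10 000), with DE = 1 + 1999 × ICC.
- Before/after: replace DE by 2 × (DE − 2000 × ICC × CAC). The CAC is the correlation of a block's level between periods. It is also not given; 0.8 is assumed.

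| Block ICC | DE | Post-only ncp | Power, 4 to 8 df | Before/after ncp | Power, 4 to 8 df |
|---|---|---|---|---|---|
| 0.004 | 8.996 | 4.32 | 89% to 96% | 5.68 | 98.4% to 99.8% |
| 0.008 | 16.992 | 3.14 | 66% to 79% | 4.47 | 91% to 97% |

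The before/after advantage depends on the CAC. At ICC 0.004 it requires 2 × (8.996 − 8 × CAC) < 8.996, that is CAC above about 0.56.

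**5. Type I error if only zones are modelled.** Null rate 22%, 20 v 20 zones, t-test on 38 df, total ICC 0.004. The correlation between zones of one block inflates the variance of a group mean by 1 + 3 × (block share of zone variance). The individual-level part is 0.996 / 500 = 0.00199.

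| Contrast | ICC at block level | Inflation | Simulated type I error |
|---|---|---|---|
| Before/after, CAC 0.8 | half | 1 + 3 × 0.0004/0.00279 = 1.43 | about 10% |
| Before/after, CAC 0.8 | all | 1 + 3 × 0.0008/0.00279 = 1.86 | about 16% |
| Post-only | half | 1 + 3 × 0.002/0.00599 = 2.00 | about 17% |
| Post-only | all | 1 + 3 × 0.004/0.00599 = 3.00 | about 28% |

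**The case against.** **The arithmetic is sound.** Four clusters follow from the stated inputs, and using t instead of the normal quantile is a refinement. This stands. A reader might infer that the sample size contains a calculation error, and it does not.

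**4 v 4 is not an announced test.** The article compares intervention with control areas overall, and stratification by department explains how the total is built. This stands too. The 80% figure bears only on comparisons within a district. It would be wrong to conclude from it that the trial has 80% power.

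**The blocks do not prove a shortfall.** At block ICC 0.004 the worst post-only figure is 89%, and the before/after contrast does better at CAC 0.8. The value 0.008 appears nowhere in the article. For ordinary geographic clustering, people in different zones of a block should not be more alike than people in one zone, so 0.008 questions the plan's own ICC as much as its unit. This largely stands. A shared navigator can add correlation of its own in the intervention blocks, so a range is still worth showing.

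**The model's cluster levels are unstated.** An article may leave them to an analysis plan, so it cannot be said that a zone-only analysis is planned. Accepted: the type I figures are conditional. The mismatch between sizing unit and layout, however, lies wholly within the article's stated design.

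**Five units is not a stated number.** The random selection is not described in detail, and the control zones are not said to be contiguous and have no navigator. This stands as a caution. Contiguity of the intervention zones and one navigator per district are explicit.

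**Conclusion.** The concern holds in limited form. The trial is sized on independent zones, whereas its selection and delivery rules make the four intervention zones of a district one unit. Five intervention units is a well-supported inference.

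- **Power.** The apparent certainty (above 99.9%) is not supported. On blocks, power lies between 89% and 99.8% at an assumed block ICC of 0.004, depending on the contrast and degrees of freedom. At an assumed 0.008 it falls to between 66% and 97%. A reader might infer that the trial is underpowered. The documents do not support that, because neither the block ICC nor the CAC is given.
- **Validity.** If the analysis ignored the block, type I error would be about 10% to 16% for the before/after contrast (CAC 0.8, half or all of the ICC at block level) instead of 5%.
- **Within district.** 4 v 4 zones give about 80% power even if zones were independent, and 90% needs 5 per group. With one intervention block and one navigator per district, the effect of navigation cannot be separated from place or person. This matters because the districts were chosen for their different characteristics and contextual factors are a stated aim.

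**What to change.** Keep the enrolment and the zones.

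1. In the primary period-by-area model, make the district-by-group block the top-level cluster, with zones nested within it, and base inference on about 4 to 8 df.
2. Restate power for five blocks per group on the before/after contrast, over a declared range of block ICCs (for example 0.004 to 0.008) and a declared CAC.
3. State how blocks and control sets are allocated, so that the number of independent units is explicit.
4. Note that 4 v 4 zones give about 80% power within a district, and report any district-specific effects descriptively.

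The cost is one more model level and a less favourable power statement. No extra zones or people are needed.

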### Study groups

#### Patient navigation intervention

The conceptual model of PN intervention was developed by Fiscella [25] to articulate the relations between program inputs, navigation activities, and specific outcomes. In this model, the author distinguished two domains of navigator’s services: instrumental/logistical, reflecting technical competence, and interpersonal/educational, reflecting the relational alliance [26] (Fig. 1).

**Fig. 1 Fig1:**
[figure not shown]
Conceptual model of patient navigation (Fiscella 2011)

The main role of the navigators is to promote CRC screening among the target population to increase participation rates in these areas. The missions of the navigators are to contact individuals living in the intervention area and invited by the screening structure and to guide them to the realization of the screening test.

Navigators’ activities will be: 1) to establish partnerships with local associations, religious places, health centers, health fairs, GPs… in order to participate in local events and to meet the target population 2) to find a committee room to meet people who are in need 3) to communicate by phone or face-to-face with the target population 4) to provide personalized assistance to each person in order to help them to overcome obstacles in the realization of the screening test (psychological, financial or logistical barriers) 5) to collect patient socio-demographic information.

#### Control group

Men and women in the control group will receive the invitation and the usual standard information document. The invitation is an administrative letter sent by all the screening management structures when men and women are scheduled to be invited to participate in the national screening program; at 50 years old and then every two years.

### Study protocol

#### Local diagnosis

We will diagnose local needs in the five selected districts before the intervention. A research team conducted semi-structured interviews with relevant stakeholders (individuals representing the target population, GPs, local actors of associations) in order to accurately assess the needs of the target population. The goal of this diagnosis was to have a better understanding of barriers and obstacles of the target population but also of the different stakeholders about the screening.

#### Recruitment and training of navigators

The strategy is to recruit and train one navigator per district. Candidates’ recruitment will be done by means of job description that will be widely diffused. The profile desired is a peer, i.e. a person corresponding to the target population of the study, living in the intervention zones. The district committees of “La Ligue contre le Cancer” (a French non-governmental organization which promotes cancer screening, gives support to patients and funds research, will be in charge of recruiting each navigator). Navigators will receive formal training for one week on all issues related to the following: the navigation process, cancer generalities, CRC screening, counseling and support to patients as needed.

#### Patient navigation intervention

Navigators will be hosted by the district committees of “La Ligue contre le Cancer” during the intervention (18 months). In each of these structures, a supervisor will be assigned to each navigator. The intervention will mainly consist of: outreaching the target population and accompanying the target population to be screened.

In order to gather information about the navigators ‘experiences (their good practice and challenges they are facing) meetings will be organized with the researchers of the study. Navigators will regularly update a field journal and a database. They will participate in the practice exchange days and develop quarterly progress reports.

#### Realistic evaluation

In this study we will use a realist evaluation approach, based on Pawson and Tilley’s work [27]. This theory-driven approach focuses evaluation on the study of what works, for whom and in what circumstances. These relationships are constructed as Context-Mechanism-Outcome configurations [28]. Considering the evaluation design, multidisciplinary teams will be associated (public health teams, human and social sciences teams and economic research teams.).

Both quantitative and qualitative data will be collected to perform the realist evaluation.

### Outcomes assessments

#### Primary outcome

To assess the effectiveness of the intervention, the primary outcome will be measured by the difference between before/after participation rates in the intervention zones and in the control zones. Other criteria will be used according to the recommendations made by the National Patient Navigation Leadership Summit (NPNLS) and published in Cancer in 2011 [29]: time to participate, participation in the whole procedure, time to complete the colonoscopy after a positive FOBT test result.

Eighteen months after the beginning of the intervention, each screening management structure, in charge of sending the invitation to individuals included in the mass screening program, will collect the participation status of the men and women included in the study. Each district structure has a database with the contact details of all individuals, eligible to receive an invitation to the national screening program. After the beginning of the intervention, the 18 month-participation rates will be measured, in selected areas. The following items will be measured: program coverage rate (percentage of people guided by navigators), screening participation rate, percentage of patients who get screened after the navigator intervention, colonoscopy completion rate.

#### Secondary outcome

The secondary outcomes for this study include 1) context of patient-related evaluation, as recommended by the Patient-Reported Outcomes Working Group (PROWG) of the Navigation program [30] 2) evaluation of evidence-informed practice 3) ethical evaluation 4) cost-effectiveness 5) organizational analysis.

A patient-related context evaluation will use measures reported by the target population in contact with navigators according to the PROWG [25]. The following fields will be explored: habits and fears regarding cancer and screening, cultural aspects, satisfaction about the intervention. An approach with questionnaires will be used, completed by semi-structured interviews. Given the lack of validated questionnaires in French, we will use a non-validated questionnaire.

In view of a future implementation of the program after its evaluation and to identify variances with the initial program, a researcher will perform an ethnographic evaluation. In total, 10 days of tracking will be done in order to know the detailed practice of the navigators, including the way they behave in order to adapt to local context for two reasons: (a) to take into consideration the potential future implementation of the program after its evaluation; b) to identify the potential variances with the initial program.

An ethical evaluation will include focus group and interviews with navigators lead by a team specializing in ethics of public health. Indeed, a project to correct social inequalities in health, through the intervention of peers, raises at least two ethical issues: 1) justice-related challenges: if justice is the guiding value of the intervention that aims to tackle health disparities, it can also trigger potentially unfair identity assignment and stigmatization. 2) Such a community-based intervention also raises challenges regarding the trust-building process.

An economic assessment of the intervention will investigate the cost-effectiveness of this program.

An organizational analysis will take the recommendations of the US program of navigation into account, to ensure comparability with other interventions [31]. The objective is to determine the conditions of implementation, sustainability and reproducibility of the program. The method of investigation is a qualitative method. Observational data will be collected at different moments: preparation of the intervention, recruitment of the navigators, during and after the intervention.

